### Participants

2.2

***Inclusion:*** Families are eligible to participate in this study if they meet all of the following criteria:(a)the child is referred to Levvel, Academic Center for Child and Adolescent Psychiatry, in Amsterdam between November 2023 and December 2024 for OCD treatment;(b)the child is between the age of 7–18 years old;(c)at time of baseline the child still meets the clinical cut-off of 16 or higher for OCD on the Child Yale-Brown Obsessive-Compulsive Scale (CY-BOCS) [31] and the child meets the DSM-5 criteria for OCD (as primary classification) as assessed with the Structured Clinical Interview for DSM-5 disorders (SCID-5 Junior);(d)psychiatric comorbidities of the child are included, provided that OCD is the primary treatment target;(e)parents report high levels of family accommodation (FA) at time of baseline (meeting the cut-off of 10 or higher on the Family Accommodation Scale Anxiety (FASA) [11]);(f)the child did not benefit from previous psychological treatment for OCD (he/she either followed 8 or more sessions of CBT or other psychotherapy), dropped out from treatment early or was unable/not motivated to receive individual treatment due to too high levels of anxiety or OCD;(g)children are allowed to use medication or selective serotonin reuptake inhibitors (SSRI's) for OCD symptoms, provided that the medication regime has been stable 4 weeks prior to participation and is expected to remain unchanged during participation.

***Exclusion:*** families meeting any of the following criteria will be excluded:(a)the child needs inpatient treatment;(b)parents are not willing to participate;(c)the child displays acute suicidality;(d)the child displays psychotic symptoms;(e)parents have insufficient mastery of the Dutch language;(f)parents or child have an estimated IQ below 75. IQ will not be tested during screening for this study, but a clinical judgement is made by the clinician during screening or intake, based on school career and medical file of the child.

### Patient recruitment and procedures

2.3

Children and their parents, referred to our academic center of expertise for youth with OCD and meeting the inclusion criteria, are contacted, and briefly informed about the research project by telephone by the researcher. During this call, the researcher (JV) conducts a first short screening to verify whether the family and the child are suitable for this research program. When a family seems eligible, a regular intake interview is planned with a clinician. After this intake interview, in which the inclusion- and exclusion criteria are checked in detail, eligible parents and children will be orally informed about the SCED study design by the researcher. Parents and children will also receive written information about the study procedures. Written informed consent will be obtained from all parents/guardians, children aged 12 and above and the teacher of the child. Only parents and children (≥12 years) who have given informed consent, will participate in this study. After informed consent has been obtained, a structured clinical interview for DSM-5 disorders (SCID-5 Junior) will be conducted with parents and children to substantiate the primary OCD classification and assess psychiatric comorbidities [32].

All participants then follow the structure of the three SCED phases: a baseline phase (A) of either four, six or eight weeks, a treatment phase (B1 and B2) consisting of 12-sessions SPACE during a period of approximately 12 weeks and a follow-up phase (C), which lasts until 6 months after the start of the baseline phase. Outcome measures are assessed with frequent brief assessments and standard clinical assessments. The majority of the instruments used in this study is part of standard clinical care and consists of psychometrically validated and sound instruments. An overview of participants procedures and randomization is provided in Fig. 1.

### Randomization

2.4

Participants will be randomly allocated to a baseline length of four, six or eight weeks, to ensure internal validity [33]. Permuted block randomization will be used with blocks of 3 and 6 and be computerized (by the data collection system Castor EDC). It is not possible to blind the researcher conducting the assessments, since the following assessments (T1 – T5, see Fig. 1) depend on the baseline period that is randomly selected. All questionnaires will be completed online to reduce researcher influence.

### Intervention

2.5

SPACE is a *parent-based treatment*, which means that the child will not be in contact with the therapist. The current study will follow the published SPACE protocol by the original developers, using an authorized Dutch translation [14,34]. SPACE consists of 12 weekly 60-min sessions. The first sessions focus on discussing the problems of the child and the rationale for the SPACE program. In later sessions, parents are taught supportive responses. Supportive responses include both acknowledgement of the child's anxious feelings as well as expressing confidence in the child's abilities to cope with these feelings. FA is then extensively explored, and a target accommodation is chosen to be modified as a first step. Modification of the parent's behavior follows a detailed plan. Parents implement the plan by informing the child about the plan with an announcement in the form of a letter to their child. Next, treatment focusses on persisting in following the plan. When the accommodation is successfully reduced, another target is chosen. The SPACE program also includes additional modules for teaching parents to deal with child's reactions to the FA reducing behavioral changes of the parent. The core component sequence and additional modules of the SPACE treatment are shown in Table 2.

**Table 2 tbl2:** Overview of the primary and secondary outcomes measures and assessment moments.

Instrument	Variable	Assessment moment and informant					
*Primary outcome measure*		Trice every week between T0 and T5 (72 assessments)					
Frequent assessment on OCD and FA	OCD and FA severity and time	P/C					

*Secondary outcome measures*		T0	T1	T2	T3	T4	T5
Children's Yale-Brown Obsessive-Compulsive Scale (CY-BOCS)^a^	OCD Symptoms	P/C					
Children's Yale-Brown Obsessive-Compulsive Scale (CY-BOCS)^a^	OCD severity	P/C	P/C	P/C	P/C	P/C	P/C
Family Accommodation Scale- Anxiety (FASA)	Family Accommodation	P	P	P	P	P	P
Family Accommodation Scale- Anxiety – Child Report (FASA-CR)	Family Accommodation	C	C	C	C	C	C
Coercive Disruptive Behavior Scale (CD-POC)	Coercive disruptive behavior child	P	P	P	P	P	P
Child Behavior Checklist (CBCL)	Emotional and behavioral problems child	P				P	P
Teacher report form (TRF)	Emotional and behavioral problems child	T				T	T
Youth Self Report (YSR)	Emotional and behavioral problems child	C				C	C
Screen for Childhood Anxiety Related Emotional Disorders (SCARED)	Anxiety Symptoms	C	C			C	C
Children Depression Inventory-2 (CDI-2)	Depressive symptoms	C	C			C	C
The EuroQol 5D (EQ-5D)	Quality of life	P				P	P
The EuroQol 5D- Youth (EQ-5D-Y)	Quality of life child	C				C	C

		Every treatment session (12 assessments)					
Outcome Rating Scale (ORS)	Well-being	P					
Session Rating Scale (SRS)	Working alliance	P					
Global Clinical Impression Severity and Improvement Scale (CGI-S & CGI-I)	Illness severity and improvement	Tp					

*Moderators and predictors*							
Demographic variables	Demographics	P					
Structures Clinical Interview for DSM-5 Disorders in children and adolescents (SCID-5 Junior)^a^	Psychiatric comorbidity child	P/C				P/C	
Social Responsiveness Scale-2 (SRS-2)	Autism Symptoms	P					
Dutch Parenting Stress Questionnaire (OBVL)	Parental stress	P				P	P
Adult Self Report (ASR)	Emotional and behavioral problems parent	P				P	P

P: Parent(s); C: Child; T: Teacher; Tp: Therapist ^a^Through online interview.

### Therapist training and treatment integrity

2.6

The therapists in our study are four experienced clinical therapists who received training (a 2-day workshop) from the developers of the SPACE treatment. The standardized Dutch treatment manual for therapists [35] and a workbook for parents is used in all treatment sessions. Protocol adherence is safeguarded via supervision once every other week by an experienced, certified SPACE supervisor. To ensure treatment integrity, all 12 treatment sessions will be video recorded. 20 % of the sessions will be randomly selected and rated on protocol adherence by two independent, trained research assistants. If participants do not give consent for video-recording during treatment, they can still participate in the study. After every treatment session, therapists complete a checklist of treatment components and report on what they discussed or practiced in the treatment session to enhance protocol adherence.

### Assessments

2.7

*Frequent assessments.* The frequent assessments obtain the primary outcome measures described as the ‘frequent measure on OCD and FA’, used for SCED analyses. During all phases (A-B1-B2-C), parents and children receive four short questions three times per week (on Mondays, Wednesdays, and Fridays) on OCD severity and FA. This will result in 72 frequent assessments for each participant (i.e. 72 assessments for each parent and 72 assessments for the child) over the total course of the study. It will result in approximately 12–24 frequent assessments during the baseline phase, 36 frequent assessments during the total treatment phase and again 12-24 frequent assessments during the follow-up phase. Participants are also asked to report any special events during the past week, each Friday during all phases. The measures are collected electronically using the smartphone application m-Path [36], designed to facilitate frequent assessments over time of participants feelings, thought, behaviors an experiences as they occur in daily life. This research methodology is often referred to as experience sampling method (ESM) [37].

*Standard clinical assessments*. The standard clinical assessments at timepoint T0-T5 and during every treatment session obtain the secondary outcomes measures, moderators and predictors of treatment response. An overview of all measures is listed in Table 2.

### Primary outcome measure

2.8

*Frequent measure on OCD and FA.* The frequent measure is a brief 4-item questionnaire on the level and time spent on OCD and FA (see Table 3). The questions are developed in collaboration with experience experts from patient organizations and families who previously received therapy for their child's OCD. Each item is rated on a 11-point scale (0–10). Both parents and the child complete the questions independently of each other.

**Table 3 tbl3:** Frequent brief assessment questions on OCD and FA for parents and children.

	Question	Scale
OCD questions parents		
1	To what extent did your child experienced obsessions and compulsions today (including the night)?	0 (*not at all*) to 10 (*to the fullest extent*)
2	How much time did your child spend on obsessions and compulsions today (including the night)?	*0 min* to *more than 8 h*
FA questions parents		
3	To what extent did you accommodate to the obsessions and compulsions of your child today (including the night)?	0 (*not at all*) to 10 (*to the fullest extent*)
4	How much time did you spent accommodating to the obsessions and compulsions of your child today (including the night)?	*0 min* to *more than 8 h*
OCD questions child		
1	To what extent did you experienced obsessions and compulsions today (including the night)?	0 (*not at all*) to 10 (*to the fullest extent*)
2	How much time did you spend on obsessions and compulsions today (including the night)?	*0 min* to *more than 8 h*
FA questions child		
3	To what extent did your parents accommodate to your obsessions and compulsions today (including the night)?	0 (*not at all*) to 10 (*to the fullest extent*)
4	How much time did your parents spent accommodating to your obsessions and compulsions today (including the night)?	*0 min* to *more than 8 h*

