## Background

1

Children and adolescents with obsessive-compulsive disorder (OCD) experience recurrent obsessions and compulsions causing significant impairments in their daily activities and family functioning. Obsessions are anxious or distress-provoking intrusive thoughts, images, or impulses. Compulsions are time-consuming ritualistic behaviors (e.g., repetitive checking, cleaning) or mental tasks (so-called cognitive compulsions, e.g., repeating sentences in one's head). OCD affects 0.5–2% of children [1,2] and is characterized by late recognition of symptoms, delayed start of treatment, and, if not treated, a chronic and disabling disease course that can disrupt development during childhood and adolescence [3].

Evidence-based first-line treatment options for pediatric OCD are cognitive behavioral therapy (CBT, including exposure and response prevention (ERP)) and pharmacotherapy (especially selective serotonin reuptake inhibitors; SSRI's). However, 40 % of children with OCD do not respond to these treatments [4,5] or drop out of treatment prematurely. In clinical trials 10 % of youth with OCD drop out of ERP treatment and 17 % drop out of pharmacotherapy [6]. In addition, little is known about treatment refusal rates in children with OCD, but it is common in clinical practice due to low motivation or high anxiety rates. Additional alternative treatment options for these unreached and often complex OCD cases are therefore urgently needed.

Increasing attention is being given to family factors that play a role in childhood anxiety and OCD [7,8], in particular to family accommodation (FA) [9,10]. FA encompasses behaviors of parents, siblings, and other caregivers to alleviate distress in the affected child. In families of children with OCD and other anxiety problems, FA is highly prevalent and significantly elevated compared with families of children without clinical anxiety disorders [11,12]. Higher FA is associated with greater severity of symptoms and poorer treatment outcomes in children and adolescents [13].

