To improve treatment outcomes for children with OCD and anxiety, Lebowitz and colleagues [14] developed an innovative parent-based (stand-alone) treatment targeting FA in relation to children's anxiety and/or OCD: *Supportive Parenting for Anxious Childhood Emotions* (SPACE). A unique advantage of the program is that SPACE is a completely parent-based treatment protocol that can be applied without cooperation of the child, and thus can be used for families of children who are reluctant or not motivated to participate in treatment or do not respond sufficiently to CBT. Parents are taught to reduce FA and to increase supportive responses towards their child.

The theoretical foundation of SPACE is based on several perspectives, such as attachment theory [15], systemic therapy, CBT and Non-Violent Resistance (NVR) [16]. Attachment theory describes the mutually interactive bond between parents and children, in which parents are inclined to protect and respond to fear or distress cues of the child and the child largely depends on the parent in dangerous or stressful situations [15]. Anxiety activates this bond; the child seeks protection from the perceived danger and the parent provides protection and regulation. Within the SPACE framework, therefore, anxiety is considered as an interpersonal and systemic construct. Protective responses of parents to their child's OCD and anxiety can be considered as repeatedly activating the attachment system. Children with OCD and/or anxiety often have difficulties with self-regulating their emotions, which can be maintained by the protective responses of parents [17]. Then, within the family, a kind of maladaptive equilibrium may arise, in which the child relies on the repeated reassuring accommodation of parents. NVR provides a framework for altering this maladaptive equilibrium. The core principle of NVR is that in situations of conflict, productively acting relies on changing one's own behavior, and not focusing on changing the other's behavior. This can help parents to avoid being drawn into the child's demanding or coercive disruptive behavior dynamics that provoke family accommodations [18,19].

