### Plan of statistical analysis for the SCED primary study parameters

3.1

In this study, the main objective is to explore the efficacy of SPACE. The primary analysis focuses on the change in the frequent measure on OCD and FA between baseline phase (A) and treatment phase (B1+B2). First, individual participants data will be separately systematically visually analyzed [61]. Next, individual data will and modelled using a generalized least squares (GLS) approach (assuming autocorrelation) [62]. To test the treatment effect on group level, a multilevel modelling approach [63] based on the examples of Shadish and colleagues (2013) [64] and Moeyaert and colleagues [63,65,66] will be used. Data from all individual participants will be included in the multilevel model and structured across a hierarchical three-level structure. Level 1 represents the frequent measurement occasions, with measures being nested within each participant. Level 2 represents the individual participants (mothers, fathers and children), with family members being nested in a family unit. Level 3 represents the family units (e.g. members of one family) included in this study. Adding time-variant predictors (the number of measurement occasion to model general time trend, a dummy-coded variable (0–1) representing the phase and an interaction term between these two) at Level 1 allows to explore for a shift in level of OCD and FA at the start of the treatment phase and the shift in trend during the treatment phase [65]. Multiple plausible multilevel models will be estimated to enhance conclusions about the treatment effect [63]. For these analyses a significance level of 0.05 is used.

Exploratory, we expect the greatest shift in OCD severity and FA level in phase B2 when parents implement their plan to reduce FA. By starting phase B2 directly after implementation of the plan we aim to explore the immediate effect of the implementation and shift in OCD and FA level during the second half of the treatment. For this purpose, an additional time predictor at Level 1 will be added to estimate shift in level and shift in trend for phase B2.

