For the secondary objectives, cross-level interactions will be added to the multilevel modelling approach to explore moderators effecting the efficacy of SPACE. To explore mechanisms of change, cross-lagged correlations will be calculated to explore the association between the frequent measure of OCD and FA over time (with respect to the direction of the association as well as the time-dependent association; [23,25]. Recent developments in the field of single-case mediation analysis (SCMA, [67]) will be used to explore mediation pathways.

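### The group-level OCD model pools the treated parents' ratings with the child's under a single phase effect, so a rating shift confined to parents would be read as change in the child's OCD

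*Protocol article*

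**What the plan says.** Section 2.8 defines the primary measure as four items, each scored 0 to 10. Two concern OCD, and parents answer both about the child: "To what extent did your child experienced obsessions and compulsions today (including the night" and "How much time did your child spend on obsessions and compulsions today (including the night". The child answers the same items about him- or herself, and "Both parents and the child complete the questions independently of each other".

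The parents are also the people treated. Section 1 says of SPACE: "Parents are taught to reduce FA and to increase supportive responses towards their child". Section 2.5 calls the treatment parent-based, "which means that the child will not be in contact with the therapist". Section 2.2 admits only families with high accommodation (FASA of 10 or more), so parental involvement in phase A is high by selection.

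For the group test, section 3.1 uses a three-level model: "Level 2 represents the individual participants (mothers, fathers and children), with family members being nested in a family unit". The Level 1 predictors it names are measurement occasion, a 0/1 phase indicator and their product, and the primary contrast is A against B1+B2. It names no informant term and no informant-by-phase term. It also says that each participant's series will be inspected visually and fitted by GLS, and that several plausible multilevel models will be estimated. For mechanisms, "cross-lagged correlations will be calculated to explore the association between the frequent measure of OCD and FA over time"; whose accommodation rating is paired with whose OCD rating is not stated.

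Results by informant are specified only in section 3.2, for the reliable change indices of the secondary measures.

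**The concern.** The parent OCD items are a proxy report by the treated person on someone else's symptoms. Part of those symptoms is hidden: section 1 counts among compulsions "mental tasks (so-called cognitive compulsions, e.g., repeating sentences in one's head". A parent must therefore rely largely on what is seen, heard or told, and some of what is seen is seen because the parent takes part in it. Treatment deliberately changes that participation, and with it possibly the parent's opportunity to observe and the standard used for rating.

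If parents' ratings move for that reason and the child's do not, a model with one average phase effect and one average phase-by-time effect reports a mixture. Letting phase effects vary randomly between persons does not help, because the average is still taken over parents and children together. Randomised baseline length (section 2.4) does not help either: it separates treatment from calendar time, but a rating shift that begins with treatment moves with the treatment start.

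The timing matters too. Section 3.1 expects the greatest shift in B2, when parents begin to reduce accommodation, and section 2.1 would read such a shift as evidence on the working mechanism. That is also when parents' involvement in symptoms changes most. Reduced OCD severity is one of the two efficacy aims, and the link from accommodation to OCD is the mechanism question, so both readings are exposed.

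**Working it through.** **The plan's own count.** Three prompts a week over 4, 6 or 8 weeks of A, 12 weeks of B and 8, 6 or 4 weeks of C: 3 × 24 = 72 per informant, with 12–24 in A and 36 in B. This agrees with section 2.7. The article states no effect size, SD or power, so no planned effect figure can be checked.

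**Weight of a parent-only shift.** Let d be the true change in the child's OCD, b the extra shift seen only in parents' ratings, and w the parents' share of the series in the pooled average. With balanced data and equal weights:

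pooled effect = w(d + b) + (1 − w)d = d + w·b

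With d = 0 and b a fall of 0.5, 1 or 2 points on the 0–10 scale (assumed values):

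| Raters | w | Apparent fall in OCD |
|---|---|---|
| two parents + child | 2/3 | 0.33 / 0.67 / 1.33 |
| one parent + child | 1/2 | 0.25 / 0.50 / 1.00 |
| two parents, child answers half the prompts | 2/2.5 = 0.8 | 0.40 / 0.80 / 1.60 |
| two parents, no child series | 1 | 0.50 / 1.00 / 2.00 |

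The third row weights by number of answers; a fitted multilevel model would weight by precision and may differ. Section 4.1 itself warns that poorly motivated children may be hard to collect data from.

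**What such a shift could do to the test.** An illustrative simulation had 25 families, two parents and one child each, baselines of 4, 6 or 8 weeks and no true change in the child. Each informant's series was fitted by AR(1) GLS, and family means were tested at two-sided 0.05. This two-stage method stands in for the three-level model. There were 300 runs per setting. Assumed on the 0–10 scale: residual SD 1.5, autocorrelation 0.3, between-person SD of the phase effect 0.7.

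| Parent-only shift | Mean pooled level shift (level-only / level + trend) | Rejections, level-only | Rejections, level + trend |
|---|---|---|---|
| none | 0.01 / 0.01 | 4% | 6% |
| fall of 0.25 | −0.16 / −0.16 | 20% | 17% |
| fall of 0.5 | −0.33 / −0.33 | 67% | 48% |
| fall of 1.0 | −0.68 / −0.65 | 100% | 94% |
| rise of 0.5 | +0.33 / +0.34 | 70% | 48% |

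The last row shows that the sign of the bias simply follows the sign of the parents' shift. The simulated shift starts on the first day of B, so it overstates the average effect of a shift that starts only in B2.

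**One way a fall could arise (illustration only).** Suppose a share s of the OCD time a parent witnesses is accommodated time, and accommodation is halved and the released part goes unseen. Parent-rated time then falls by s × 0.5. For s = 0.3, 0.5 or 0.7 that is 15%, 25% or 35%. Times 2/3 (equal baseline ratings), the pooled fall is 10%, 17% or 23%. These hold only while the reduction is in force. B1 precedes any plan; if B2 were half of the treatment phase, the average over B would be about 5%, 8% or 12%. The documents give none of these shares.

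**The case against.** A reader might infer that parents can rate only what they witness, that SPACE takes them out of the rituals, and that the pooled effect is therefore biased towards benefit. The documents do not support that chain.

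- No section limits parents to what they see. Table 3 asks for a judgement of the whole day, and parents may draw on what the child says or what they overhear.
- Parents reduce one chosen accommodation and then another while increasing supportive responses (section 2.5). They do not withdraw from the child.
- Hidden symptoms are hidden in A and B alike. A constant blind spot does not bias an A-to-B contrast; only a change in observation or rating standard does.
- The direction is open. Psychoeducation and charting in B1 could make parents notice more, and disruptive reactions to reduced accommodation, for which the programme has modules, could make OCD more visible.

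These points stand, and they limit the claim to a possible bias of unknown sign.

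There are also safeguards. Section 3.1 analyses each participant's series individually, including the child's. The CY-BOCS is clinician-rated at T0–T5. Section 3.2 reports reliable change per informant. They are partial: individual fits and change indices give no informant-specific group test, and the CY-BOCS is secondary and built partly on parent report.

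An informant term may already sit in a fuller analysis plan, or among the several models that section 3.1 foresees. That is possible, and then only the reporting needs attention. But the article does state the model and its predictors, and the comment is on that stated model.

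On mechanism, section 3.1 does not say that FA and OCD will be paired within the same parent, and the analysis is exploratory. A same-day rating artefact chiefly produces same-day association; it is not shown to produce accommodation leading OCD. What remains is that same-rater pairs share a rater and should be recognisable as such.

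**Conclusion.** The point holds as a possible bias in the primary group-level OCD estimate, not as a demonstrated one. The article has treated parents rate a child outcome that is partly hidden, the treatment changes their involvement in it, and the stated group model averages their ratings with the child's without separating informants. A benefit-directed bias is plausible, but sign and size are unknown.

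What can be stated firmly is the weight: two thirds of any parent-only shift with two parents and a child, half with one parent, and more where children's answers are missing. This rests on equal weighting and balanced series. The rejection rates and percentage falls rest on assumed inputs; they show that a modest shift could matter, not that one will occur.

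A reader might go further and hold that the child's OCD may be said to have fallen only if the child-rated items show it. The documents do not support so strict a rule: section 4.1 describes some of these children as having low insight and low motivation, so their ratings are not a clean reference either. The change is worth making before the data are analysed, because it costs little and decides how the OCD result can be read.

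**What to change.** In section 3.1:

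1. Add informant (parent/child), informant-by-phase and informant-by-phase-by-time terms to the OCD multilevel model, with the matching terms when the B2 predictor is added.
2. Report the group OCD effect separately for parent-rated and child-rated items beside the pooled effect, with intervals, and state that an effect seen only in parents' ratings will be interpreted with caution.
3. In the exploratory cross-lagged and mediation analyses, also report parent-rated FA paired with child-rated OCD, and label pairs from the same rater as such.

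Both informants' ratings are already collected, so this changes wording and analysis only. The cost is a wider interval for the child-rated effect, because it rests on one rater per family and possibly on more missed prompts.
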